To address these issues, the ‘Treatment of ADHD with Care as usual versus an Elimination diet’ (TRACE) study has been developed. This is the first RCT (two armed, 50:50 ratio) to determine the short- and long-term effectiveness and cost-effectiveness of an ED compared to an active control group (a healthy diet). Care As Usual (CAU) is included as a comparator arm. During the initial 5 weeks of the study, participants receiving a dietary treatment are not allowed to start any other treatment. Also, medication prior to the dietary treatment has to be discontinued no later than 1 week before start of the diet. The study will examine effects on both ADHD and emotion dysregulation, given that an ED showed equal effects on ADHD and its common comorbidity Oppositional Defiant Disorder (ODD) (i.e. children with ODD are more likely to experience emotion dysregulation problems) [14]. We will substantially improve upon previous studies by comparing an ED with a healthy diet (based on the World Health Organization (WHO) guidelines), comparing the two dietary treatments with CAU, examining the short- and long-term effects (i.e. after 5 weeks and 1 year) and cost-effectiveness, measuring the nutritional quality of the consumed diets and including blinded and objective measurements.

The primary objective of the TRACE study is to quantify the short-term (after 5 weeks) effectiveness in reducing ADHD and emotion dysregulation symptoms of an ED compared to an active control group (a healthy diet) in children aged 5–12 years with ADHD: we assume that the ED is more effective than the healthy diet. Secondary, the study aims at examining the long-term (after 1 year) effects in reducing ADHD and emotion dysregulation symptoms. Moreover, the study aims at examining the short- and long-term effects of an ED compared to an active control group (a healthy diet) in reducing secondary outcome measures related to ADHD such as cognitive outcomes, motor activity and sleep pattern. In addition, the study aims to identify potential moderators and mediators (e.g. socioeconomic status (SES), ethnicity, comorbidity) of the short- and long-term response to dietary treatments, and to examine the nutritional quality of the attained diet and health of children treated with a dietary treatment compared to CAU. Finally, the study aims to examine the cost-effectiveness of the dietary treatments compared with CAU.

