##### Cost measurements

Healthcare resources use, patient and family costs and productivity losses (absence from work of parents) as a consequence of the child’s psychiatric disorder are measured using the Dutch ‘Trimbos and iMTA questionnaire on Costs associated with Psychiatric illness’ (Tic-P questionnaire) [49]. Validity and reliability have been established [49]. The number of all health care contacts is registered with a 3 month recall period. These data are used to calculate the cost-effectiveness of the dietary conditions compared to CAU at 12 months of follow-up.

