### Statistical analyses

All primary analyses will be Intention To Treat. The primary outcome will be measured as an ordinal variable with five categories. Therefore, the effect of the intervention will be measured in terms of odds ratio, comparing odds for reducing ADHD symptoms and emotion dysregulation symptoms in the elimination diet group with the corresponding odds in the healthy diet group. Multiple logistic regression analyses will performed to compute the odds ratio and 95% confidence intervals, using ordinal logistic regression analysis. The CAU group will be used as a reference group.

Differences in continuous outcome measures between the dietary trajectories will be determined with analyses of ANCOVA. The follow-up value (T1, after five weeks) will be added as the dependent variable and the baseline value will be added as covariate. The two dietary groups will be compared on all outcomes at T1, using T0 scores as covariates. Clinical significance will be estimated using the partial eta squared effect. The CAU group will be used as a reference group.

In addition, a repeated measures ANOVA will be performed. First, the whole sample will be used (Intention to Treat) to determine whether adding a dietary treatment has beneficial outcomes on costs and effects of the whole treatment trajectory after 12 months (regardless of continuing the dietary treatment after 5 weeks or not). Next, per-protocol and post-hoc analyses will be performed using repeated measures ANOVA where the main outcome measures will be compared across the three conditions (i.e. elimination diet; healthy diet; CAU). Also, we will determine how many children adhered to the diet after 12 months, whether the intervention effects maintained after 12 months, which products are eliminated from the diet after 12 months and the nutritional quality of the attained diet after 12 months.

Finally, two moderator analyses will be performed: one comparing dietary responders versus non-responders (predicting respondership) and another comparing children/families adhering to a dietary treatment versus children/families that are not able to do so (predicting adherence). Both moderator analyses will be performed to compare children/families after 5 weeks and after 1 year of treatment.

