For the cost-effectiveness analysis, all cost data will be accumulated over the 12 months period. Cost differences between the two dietary conditions and CAU will be compared. Incremental cost-effectiveness ratios will be calculated by dividing cost differences between treatments by differences in Quality Adjusted Life Years, as estimated from EQ-5D scores. Uncertainty analysis using 5000 bootstraps will be performed and cost-effectiveness planes and cost-effectiveness acceptability curves will be plotted.

The impact of missing data on the outcome measurements will be evaluated using different methods, such as Last Observation Carry Forward (LOCF) and Multiple Imputation (MI).

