## Discussion

The goal of the present paper was to describe the rationale, study design and methods of the TRACE study: an ongoing two arm randomized controlled trial comparing the short and long term effects of an elimination diet and a healthy diet in children with ADHD. A comparator arm including children being treated with Care as Usual (CAU) is used to compare the effects found in both dietary groups. Results from this study are expected to offer insight into the short-term (i.e. five weeks) and long-term (i.e. one year) effectiveness in reducing ADHD and emotion dysregulation symptoms and measures related to ADHD (e.g. cognitive outcomes) of an elimination diet compared with an active control group (healthy diet), possible moderators of the response to dietary treatment, nutritional quality of the attained diet and cost-effectiveness of the dietary treatments compared with CAU.

So far, several studies examined the effects of food on ADHD symptoms [11–13]. However, studies examining the effects of dietary treatments in children with ADHD suffered from several limitations (e.g. long-term effects are unknown). The TRACE study aims to fill these knowledge gaps and to take into account limitations of previous studies.

It is estimated that recruitment for the trial (*N* = 81 in both dietary groups; *N* = 60 in the comparator arm) will be completed in December 2020. Data collection for the follow-up measurements is anticipated to be completed by December 2021.

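### The protocol names two different cost-effectiveness comparators, does not fix which pairs enter the ICER, and never explicitly plans the randomised elimination-diet-versus-healthy-diet ratio

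*Protocol article*

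**What the plan says.** The protocol article speaks to the cost-effectiveness comparator in several places.

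- **Background, paragraph introducing TRACE:** the trial is to "determine the short- and long-term effectiveness and cost-effectiveness of an ED compared to an active control group (a healthy diet". The comparator here is the healthy diet.
- **Background, paragraph listing the objectives:** "Finally, the study aims to examine the cost-effectiveness of the dietary treatments compared with CAU". The comparator here is CAU.
- **Outcomes, Cost measurements:** "These data are used to calculate the cost-effectiveness of the dietary conditions compared to CAU at 12 months of follow-up". Again CAU.
- **Statistical analyses, 12-month analysis:** the question is "whether adding a dietary treatment has beneficial outcomes on costs and effects of the whole treatment trajectory after 12 months". No ED-versus-HD contrast is named, and the two diets could be taken separately or pooled.
- **Statistical analyses, cost-effectiveness paragraph:** "Cost differences between the two dietary conditions and CAU will be compared", followed by "Incremental cost-effectiveness ratios will be calculated by dividing cost differences between treatments by differences in Quality Adjusted Life Years", with QALYs estimated from EQ-5D. The ICER sentence refers only to treatments in general. It names no pair, no reference option and no ordering. Uncertainty is to be shown with 5000 bootstraps, planes and acceptability curves.
- **Data monitoring:** the stopping rule is justified by whether the diets could match CAU on effectiveness and cost-effectiveness.
- **Discussion:** the expected results include the "cost-effectiveness of the dietary treatments compared with CAU".

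Under Study design, Randomization, only the two diets are randomised against each other. CAU became a non-randomised comparator after 17 inclusions, and under Procedures families choose between the diet arms and CAU.

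**The concern.** One sentence sets a question (ED against HD) that the later text does not explicitly plan to answer. If Cost measurements governs the analysis, the first-stated cost-effectiveness question has no planned ICER. If the general wording in Statistical analyses governs, the pairs are open and could be settled after the results are known.

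Two things are at stake. First, ED versus HD is the only cost and QALY contrast protected by randomisation. Every diet-versus-CAU ratio compares families who wanted a diet with families who did not, so differences in cost and QALY may partly reflect who chose what. Second, the trial's own rationale is that an ED must be separated from general dietary improvement. The same holds for value for money: whether the ED and its long reintroduction phase buy anything beyond a healthy diet requires the increment between the two diets, which ratios against a third option do not supply.

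**Working it through.** There is no cost, QALY, threshold or ICER figure in the document to reproduce. The check therefore has two parts.

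**1. Comparator named in each section**

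| Section | Comparator | Pairs fixed? |
|---|---|---|
| Background, introduction of TRACE | HD | ED v HD |
| Background, closing aim | CAU | diets v CAU |
| Cost measurements | CAU | diets v CAU |
| Statistical analyses, 12-month analysis | not named | no |
| Statistical analyses, costs | the two diets and CAU | no: each diet, pooled diets or three-way |
| Statistical analyses, ICER | not named | no |
| Data monitoring, stopping rule | CAU | diets v CAU |
| Discussion | CAU | diets v CAU |

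HD appears as the cost-effectiveness comparator once. CAU is the stated comparator in four places. The analysis sentences fix neither.

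**2. What diet-versus-CAU ratios can and cannot show**

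All increments below are assumptions for illustration, in euro and QALYs relative to CAU. ICER = cost difference / QALY difference.

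*Case A.* HD +300 and +0.020; ED +400 and +0.018.
- HD v CAU: 300 / 0.020 = 15,000 per QALY.
- ED v CAU: 400 / 0.018 = 22,222 per QALY.
- ED v HD: cost 400 - 300 = +100; QALY 0.018 - 0.020 = -0.002. ED is dominated.

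*Case B.* HD as in A; both ED increments multiplied by 2.5, so +1,000 and +0.045.
- HD v CAU: 15,000, unchanged.
- ED v CAU: 1,000 / 0.045 = 22,222, unchanged.
- ED v HD: (1,000 - 300) / (0.045 - 0.020) = 700 / 0.025 = 28,000 per QALY.

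The same two ratios against CAU fit both cases, so the ratios alone do not determine the comparison between diets.

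*Case C.* HD +500 and +0.010; ED +1,100 and +0.015.
- HD v CAU: 500 / 0.010 = 50,000. ED v CAU: 1,100 / 0.015 = 73,333.
- ED v HD: 600 / 0.005 = 120,000 per QALY.

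**Point estimates.** If cost and QALY differences are reported for each diet separately, ED v HD follows by subtraction, as done above. If the diets are pooled against CAU, it does not.

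**Uncertainty.** With independent arms, Var(ED - CAU) + Var(HD - CAU) = Var(ED) + Var(HD) + 2 Var(CAU), whereas Var(ED - HD) = Var(ED) + Var(HD). The shared CAU arm makes the two published differences correlated. Two separate planes or acceptability curves against CAU therefore do not give the uncertainty of ED v HD. That needs its own bootstrap output.

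**The case against.** The strongest reply is that nothing is excluded. The ICER sentence speaks of treatments without naming pairs, and the cost sentence can be read as a three-way comparison. A reader might infer that ratios will be taken against CAU only and that ED versus HD will never be estimated. The documents do not support that: no section plans the contrast explicitly, and none rules it out. Nor do they say that a separate ratio will be formed for each diet. This part of the reply stands.

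A reader might also infer that a dominated diet would go unnoticed and be declared cost-effective. That is too strong. Cost differences, QALY differences and planes are planned, and if they are given per diet, dominance in the point estimates is visible by subtraction. What is not recoverable is the joint uncertainty between the diets.

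The reply adds that CAU is the comparator in the formal list of aims, that comparing diets with usual care is a coherent question, and that the Background sentence is mere framing. The first two are right, so CAU should not be demoted. The third is weaker: the sentence is a claim about what this RCT will determine, and it names the one comparison that randomisation supports.

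Finally, a condensed article may leave health-economic detail to a fuller document. That covers technique. It does not cover two conflicting comparators within the article.

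**Conclusion.** The concern holds in a limited form. The article names HD as the cost-effectiveness comparator in one place and CAU in the others, and its analysis section does not settle which pairs enter the ICER. The randomised ED-versus-HD ICER is not explicitly planned anywhere. Diet-versus-CAU ratios alone would not supply it or its joint uncertainty, and they rest on a self-selected arm.

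The stronger reading, that this ICER is definitely omitted or that a dominated diet would definitely be called cost-effective, is not established.

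No size can be derived from the document. The illustrations rest wholly on assumed increments: with identical ratios against CAU, ED ranges from dominated (Case A) to 28,000 per QALY over HD (Case B), and in Case C a ratio of 73,333 against CAU goes with 120,000 against HD. They show what is possible, not what is likely; the dominance case assumes fewer QALYs with ED, whereas the trial expects ED to work better on symptoms. The point is worth correcting before analysis, and it does not touch the primary outcome.

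**What to change.** In the cost-effectiveness paragraph of Statistical analyses:

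1. Add the randomised ED-versus-HD cost difference, QALY difference and ICER, with its own bootstrap plane and acceptability curve.
2. Keep the diet-versus-CAU ratios alongside it, state whether they are for each diet or for the diets pooled, and label them as non-randomised.
3. Report the three options incrementally, so that a dominated diet is identified.
4. Align the two statements in the Background, Cost measurements and the Discussion with this set of comparisons.

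The cost is small. Table 3 already schedules EQ-5D at T0 to T4 and the Tic-P cost questionnaire at T1 to T4, neither is among the instruments dropped for CAU, and the 5000 bootstraps are already planned. No new data are needed, only a little more analysis and reporting.

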### Study design

#### Randomization

Originally, the TRACE study was a three arm randomized controlled trial: participants were randomized to an elimination diet, healthy diet or CAU. However, randomization across a dietary intervention versus CAU proved not feasible. Parents usually had a strong preference towards either a dietary intervention or CAU. This resulted in an extremely slow inclusion rate, a high number of drop-outs and thereby unrepresentative groups of CAU. Therefore, after inclusion of 17 participants, the design was changed into a two arm randomized controlled trial (elimination diet vs. healthy diet) with a non-randomized comparator arm (CAU). Participants interested in a dietary intervention are randomized (50:50) to either an ED or a healthy diet with randomization within each participating center. Randomization by means of minimization is performed, including sex and age as factors, resulting in four groups. Within each group, blocked randomization is used (block size eight). The non-randomized comparator arm includes children who are being treated with CAU. Researchers disclose the group allocation to parents via a sealed envelope. Participants, researchers and dieticians are aware of treatment allocation. Researchers who will code the behavior observation (see secondary outcomes) are blinded to group allocation and time of assignment.

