### Procedures

Families who are interested to participate in the TRACE study are informed via telephone and information letters (sent via e-mail). Families can choose whether they want to participate in the dietary treatment arms or the CAU arm. If they choose a dietary treatment, they will be randomly assigned to either the elimination diet or the healthy diet.

If the eligibility criteria are met, parents are invited for an intake with a researcher to explain further details of participation, plan appointments and to disclose which diet the child is randomized to via a sealed envelope. Both parents fill out a written informed consent for the TRACE study (Additional file 1). If children are 12 years old, they also need to sign the consent forms. In addition, teachers are informed about the study via e-mail and general practitioners via postal letters.

Assessments will take place at baseline (T0), after five weeks of treatment (T1), after four (T2), eight (T3) and 12 (T4) months after start of treatment (i.e. dietary treatment or CAU). T0 will be scheduled within two weeks prior to the start of the treatment. Medication treatment prior to the dietary treatment has to be discontinued no later than one week before start of the diet. T0, T1 and T4 assessments will take place at one of the two participating sites. For the T2 and T3 assessments, parents are asked to fill out questionnaires online. Teachers are asked to fill out online questionnaires at T0, T1 and T4. Figure 1 depicts a flowchart on recruitment and procedure of the study.

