**Secondary outcomes**		
Blinded ADHD assessment	T0, T1, T4	DB-DOS
Parent & teacher comorbidity ratings	T0, T1, T4	SDQ, CSBQ, BRIEF, UPPS-P, EDI
Cognitive performance	T0, T1, T4	COTAPP
School performance	T0, T4	Monitoring system Dutch education
Motor activity and sleep pattern	T0, T1, T4	Actigraph
Physical measurements	T0, T1, T4	Weight, height, blood pressure, heart rate
Somatic complaints	T0, T1, T2, T3, T4	Pittsburgh side-effects rating scale
Sleep problems	T0, T1, T2, T3, T4	5-item questionnaire
Quality of life	T0, T1, T2, T3, T4	EQ-5D
Food consumption & eating habits	T0	Questionnaire dietary pattern
	T0, T4	Nutritional assessment (‘Eetmeter’)
Nutritional quality	T0, T2, T3, T4	Nutritional assessment (‘Eetmeter’)^b^
	T0, T1, T2, T3, T4	Expert view
	T0, T1, T4	Blood sample
Carer-related quality of life	T0, T1, T2, T3, T4	CarerQol, PSQ
Parenting styles and family functioning	T0, T1, T4	FFQ, BSBP
Adherence	T1, T4	Morisky Adherence Scale, food diary, separate questions
Satisfaction	T1, T4	GGZ-Thermometer
Cost measurements	T1, T2, T3, T4	Tic-P

*WPPSS-III* Wechsler Preschool and Primary Scale of Intelligence, *WISC-III* Wechsler Intelligence Scale for Children, *GHQ* General Health Questionnaire, *SWAN* Strengths and Weaknesses of ADHD-symptoms and Normal-behaviors (SWAN) rating scale, *SDQ* Strength and Difficulties Questionnaire, *DB-DOS* Disruptive Behavior Diagnostic Observation Schedule, *CSBQ* Children’s Social Behavior Questionnaire, *BRIEF* Behavior Rating Inventory of Executive Function, *UPPS-P* Urgency, Premeditation, Perseverance, Sensation seeking, and Positive urgency Impulsivity scale, *EDI* Emotion Dysregulation Inventory, *COTAPP* Cognitive Task Application, *PSQ* Parenting Stress Questionnaire, *EQ-5D* EuroQol Five Dimensions Health Questionnaire, *FFQ* Family Functioning Questionnaire, *BSBP* Brief Scale of Parental Behavior, *Tic-P* Trimbos and iMTA questionnaire on Costs associated with Psychiatric illness’

^a^T0 baseline; T1 five weeks after baseline; T2 four months after baseline; T3 eight months after baseline; T4 12 months after baseline. ^b^ Only parents of healthy diet participants who continue the diet after five weeks, register food consumption at T2 and T3

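### The cost-effectiveness ratio is set out with no adjustment of QALYs for baseline EQ-5D, although its comparator is a care-as-usual arm that families choose

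*Protocol article*

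**What the plan says.** All references are to the protocol article.

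- **Estimator (Statistical analyses).** "Incremental cost-effectiveness ratios will be calculated by dividing cost differences between treatments by differences in Quality Adjusted Life Years, as estimated from EQ-5D scores". The differences are called neither raw nor adjusted, and no covariate is named.
- **Contrast (Statistical analyses).** "Cost differences between the two dietary conditions and CAU will be compared". The Cost measurements section and the last study aim in the Background also set the diets against CAU.
- **Uncertainty (Statistical analyses).** "Uncertainty analysis using 5000 bootstraps will be performed and cost-effectiveness planes and cost-effectiveness acceptability curves will be plotted".
- **Baseline adjustment that is stated (Statistical analyses, ANCOVA paragraph).** "The two dietary groups will be compared on all outcomes at T1, using T0 scores as covariates". The paragraph adds that CAU serves as reference group, without saying whether the T0 covariate applies there. Either way the time point is T1.
- **EQ-5D schedule (Table 3).** "Quality of life T0, T1, T2, T3, T4 EQ-5D", with the timing "T0 baseline; T1 five weeks after baseline; T2 four months after baseline; T3 eight months after baseline; T4 12 months after baseline". The section on measurements in the CAU arm lists the questionnaires dropped for that arm, and EQ-5D is not among them.
- **How CAU is formed.** Randomization: "The non-randomized comparator arm includes children who are being treated with CAU". Procedures: "Families can choose whether they want to participate in the dietary treatment arms or the CAU arm".

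**The concern.** A 12-month QALY is an area under the utility curve that starts at T0. Baseline utility therefore affects it in two ways: directly, as the first point of the curve, and indirectly, because children with higher utility at T0 tend to have higher utility later. If two groups differ at T0 and the QALY difference is not adjusted, part of that difference appears as an effect of treatment.

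In a randomized comparison such a gap is chance. In the comparison that the cost-effectiveness analysis relies on, it need not be. The Randomization section reports that parents usually had a strong preference for either diet or CAU, and that this preference is why randomization to CAU was abandoned. Families who choose a diet may well differ at baseline from those who choose CAU, in either direction.

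What is at stake is the denominator of the ratio, and with it the plane and the acceptability curve. Resampling children from self-selected groups reproduces the gap between the groups in every replicate, so the bootstrap shows the spread around a shifted centre and gives no sign of the shift.

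**Working it through.** **Figures in the plan.** The article gives no QALY figure to reproduce: no EQ-5D standard deviation, between-visit correlation, expected baseline gap or expected QALY gain. Its power figures concern respondership and do not bear on this point. The visit times and group sizes below come from the article; the rest is assumed and shown as a range.

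**Step 1: weight of each visit.** Assume the usual trapezoidal area. Visits are at 0, 5/52, 4/12, 8/12 and 1 year (Table 3). Each visit's weight is half the sum of its adjacent intervals:

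- T0: (5/52)/2 = 0.048
- T1: (4/12)/2 = 0.167
- T2: (8/12 − 5/52)/2 = 0.285
- T3: (1 − 4/12)/2 = 0.333
- T4: (1 − 8/12)/2 = 0.167

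The weights sum to 1, so the direct share of T0 is about 5%.

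**Step 2: share of a T0 gap carried over.** Assume equal variance at each visit and the same correlation ρ between any two visits. The slope of the 12-month QALY on T0 utility is then 0.048 + 0.952ρ. This is the share of a T0 gap that adjustment would take out of the difference.

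**Step 3: precision.** In units of the utility variance, the QALY variance is ρ + (1 − ρ) × 0.250, where 0.250 is the sum of the squared weights. The squared correlation of QALY with T0 is r² = slope² / variance. Adjustment multiplies the SE by √(1 − r²).

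| Assumed ρ | Share carried over | QALY error for an assumed T0 gap of 0.05 | SE ratio after adjustment |
|---|---|---|---|
| 0 | 0.048 | 0.002 | 0.995 |
| 0.3 | 0.334 | 0.017 | 0.875 |
| 0.4 | 0.429 | 0.021 | 0.82 |
| 0.5 | 0.524 | 0.026 | 0.75 |
| 0.6 | 0.619 | 0.031 | 0.67 |
| 0.7 | 0.714 | 0.036 | 0.58 |
| 0.8 | 0.810 | 0.040 | 0.48 |

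**Step 4: scale of a 0.05 gap.** With 81 children on a diet and 60 on CAU, and an assumed utility SD of 0.15 to 0.20, the SE of the T0 difference is SD × √(1/81 + 1/60) = 0.026 to 0.034. A 0.05 gap is thus about the size that chance alone can produce (1.96 × 0.026 = 0.05). A selection effect of that size would not stand out in a baseline table.

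**Step 5: effect on the ratio (illustration only).** Take an assumed cost difference of 1000 and a true gain of 0.05 QALY, a ratio of 1000/0.05 = 20,000. With ρ = 0.5 the error is 0.0262 QALY. The ratio becomes 1000/0.0762 ≈ 13,100 or 1000/0.0238 ≈ 42,000, depending on which group was healthier at T0.

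**The case against.** The strongest objection is that the article does not say the differences are unadjusted. The sentence on the ratio is its ordinary definition, and a regression-adjusted QALY difference fits it equally well. The article is condensed, and covariates of an economic model are often left to the analysis plan. This stands as a limit on the wording: a reader might infer that the sponsor has decided on raw differences, and the text does not support that. The point survives because the article otherwise fixes the analysis (the ratio, the contrast, the number of bootstraps, the plots), states T0 adjustment elsewhere, and limits that rule to T1. Followed as written, the plan adjusts nothing at 12 months. The whole-sample repeated measures ANOVA of 12-month costs and effects does not fill the gap, since nothing links it to the ratio.

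Second, a reader might infer that a baseline gap is counted in full as QALYs. It is not. The direct share is about 5%; everything beyond that depends on a correlation the documents do not give, and near zero correlation both bias and precision loss are negligible. The formula also assumes that a gap between groups fades as differences between children within a group do, which need not hold for self-selected groups.

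Third, a reader might infer that the bootstrap is invalid throughout. For elimination diet against healthy diet it is valid: allocation is random, and resampling already includes chance variation at T0.

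Fourth, T0 adjustment does not cure confounding by family choice. That is correct, and it limits what the fix can claim.

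**Conclusion.** The concern holds in a limited form. As the article sets it out, the 12-month QALY difference has no stated adjustment for T0 EQ-5D, and the main economic contrast is against a non-randomized arm.

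- **Each diet against CAU.** A baseline utility gap would bias the QALY difference by about a third to four fifths of its size at assumed correlations of 0.3 to 0.8. An assumed gap of 0.05 gives about 0.017 to 0.040 QALY, and the plane and acceptability curve would be centred on the shifted value.
- **Elimination diet against healthy diet.** There is no bias. The cost is precision: the SE could be about 12% to 52% smaller with adjustment over the same range.

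These sizes rest on trapezoidal QALYs, equal variances, equal correlation between visits and an assumed gap. Neither the direction nor the existence of a gap is known from the document. The primary outcome is unaffected. The change is worth making because the economic conclusion depends on this contrast and the covariate is already scheduled in all three groups.

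**What to change.** In the cost-effectiveness paragraph of Statistical analyses:

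1. Estimate the 12-month QALY difference by regression on treatment group with T0 EQ-5D utility as covariate, plus centre, sex and age, which already enter the randomization.
2. Refit this model within each of the 5000 bootstrap replicates, resampling each child's costs and QALYs together, and use the adjusted difference in the ratio, the plane and the acceptability curve.
3. Describe each diet against CAU as a non-randomized comparison in which residual confounding remains after this adjustment.

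If the analysis plan already does this, a sentence in the report saying so is enough. The cost is a few lines of text and one model inside a bootstrap that is already planned; no new measurements are needed.
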